### Study Design

The PoC was structured as a controlled longitudinal pilot study, with a before-and-after design, where observations were run on a series of enrolled individuals, who received the intervention described later, with data collected before and after the installation and use of the technical solution. The goal of trial evaluation was to demonstrate the viability of engAGE technology integration into everyday life to counteract cognitive decline. As secondary outcomes, the impact on the social dimension and quality of life of end users was evaluated. Moreover, acceptance over 6 months and the usability of proposed solutions were evaluated to understand the feasibility of the intervention. Despite the choice to structure the PoC as an RCT in order to provide more robust evidence on feasibility and efficacy [22,23], a formal sample size calculation was not performed. Practical constraints within the project were considered while deciding the number of end users to enroll. In fact, recruitment timelines, availability of rooms and professionals, and technical equipment represented practical limits for the study feasibility. After considering these constraints, the sample size for the PoC was set to 80 primary end users: 50 (62.5%) in the experimental group (EG) and 30 (37.5%) in the control group (CG).

In Italy, end users were recruited from the Neurology Unit and Alzheimer Assessment Unit (Memory Clinic) and from the Alzheimer daycare center of the Istituto di Ricovero e Cura a Carattere Scientifico – Istituto Nazionale di Riposo e Cura per Anziani (IRCCS INRCA). The research team could communicate with potential participants of previous projects and initiatives, as well as with other people who might have been be interested in contributing to the project evaluations. This method made it possible to be in contact with clients met before and with whom a relationship of trust was already established.

In Norway, participants were recruited from two daycare and housing centers in the city of Arendal. The first one, Solhaug, is a daycare center for old residents living in their own homes, while the second one, Plankemyra, is a combined housing and daycare center.

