### Recruitment

A specific number of people were recruited for the study via health care institutions or health care organizations. Potential participants were evaluated by eligible professionals through face-to-face interviews to verify that eligibility criteria were met. Those who did not meet the criteria or declined participation were excluded. The remaining participants were randomly assigned to the EG or the CG. A randomization technique, conducted by a statistician, based on a single sequence of random assignments was adopted. A list of random numbers was generated by the computer, while subjects were assigned a number based on their order of inclusion in the study. According to this technique, in Italy and Switzerland, the 30 subjects were randomly assigned to one of the two study groups (n=20, 66.7%, in the EG and n=10, 33.3%, in the CG), while in Norway, 20 subjects were equally assigned to the two groups. Next, for both groups, we took careful note of who were lost to follow-up, who discontinued intervention, or who were excluded from analysis. The procedure adopted is summarized in Figure 3.

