Outcomes that concern efficacy of the engAGE intervention were considered exploratory and dealt with the metrics about cognitive capacity, quality of life, social dimension, and stress and care load relief (for caregivers). In particular, to explore the potential efficacy, changes in these domains before and after the intervention were analyzed. Paired *t* tests (for normally distributed data) or Wilcoxon signed-rank tests (for nonnormally distributed data) were used to compare pre- and postintervention scores within each group, while independent samples *t* tests or Mann-Whitney U tests were performed to assess between-group differences in change scores. Moreover, effect sizes (Cohen d or Cliff δ) were calculated to quantify the magnitude of any observed differences. Due to the nature of the PoC, this study was not powered to detect statistical significance. *P* values will be reported without adjustments for multiple comparisons and interpreted with caution. All analyses were planned for descriptive purposes, and only participants with at least 80% of adherence to the intervention were considered for analysis.

The aforementioned analyses were also applied to acceptance and usability measurements (ie, UTAUT and SUS scores) that provided insights into the primary goal of the study: the feasibility of the intervention. Data from the ML service were analyzed to correlate physical activity, sleep parameters, game scores, and self-assessment data. Longitudinal data analysis techniques (eg, mixed effects models) were used to analyze changes in these parameters over time and assess potential correlations with cognitive and quality-of-life outcomes.

The first step in the data analysis dealt with the description of the sample. Continuous variables will be reported as either the mean (SD) or the median (IQR) on the basis of their distribution (assessed using the Kolmogorov-Smirnov test). Categorical variables will be expressed as an absolute number and percentage. Mann-Whitney U tests (for nonnormal distribution) or chi-square tests (for normal or nonnormal distribution) were used to compare independent and dependent variables between the pre- and postintervention conditions, in addition to simple descriptive statistics (means, medians, and SDs, as appropriate).

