## Results

Recruitment started in October 2023 and continued until April 2024, when there was still time to attend 80% of the trial in the three sites. At the end of recruitment, 40 (81.6%) of the total 49 older adults with MCI were assigned to the EG and 9 (18.4%) to the CG. The PoC started in November 2023 and ended in July 2024. The start and end dates were different across countries because of the various difficulties encountered in organizing the trial and recruiting end users in each site. The efficacy of the engAGE platform will be demonstrated on the basis of the improvement or maintenance of cognitive capacity. In addition, the effects on the quality of life and social connectedness of primary end users, as well as the reduction in the care load and stress of caregivers, will contribute to determining the importance of the platform. Furthermore, the feasibility of the engAGE intervention will be assessed on the basis of the usability and acceptance of the platform, both measured through standardized quantitative scales. Data analysis was completed at the end of 2024, and the results will be published at least by 2026.

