### Limitations

Although the engAGE project aims to represent an important step toward developing integrated digital health solutions for older adults with MCI, several limitations should be acknowledged. Despite the study being structured as an RCT, the sample size was not computed, and the number of end users enrolled was relatively small (N=80), limiting the generalizability of findings to larger populations. Due to the focus on the feasibility and initial efficacy of the intervention, the findings should be used to inform future sample size calculations and refine intervention protocols for future studies that aim to demonstrate the efficacy of the engAGE platform. Participants were recruited from health care organizations and daycare centers located in city areas, introducing a potential bias: people with less access to health and digital services were not considered. However, to make results more generalizable, the study was conducted across three European countries (Italy, Norway, and Switzerland) that show differences in cultural and health care contexts.

The duration of the study (ie, 6 months) was minimal, as it was unlikely to observe significant changes in cognitive capacity or the caregiver burden. Moreover, ML algorithms are designed to personalize interventions based on user data, and the study duration could not be sufficient to fully profile individual preferences or needs, making the personalization inefficient. Finally, the complexity of the platform due to the integration of several technologies, services, and ML algorithms introduced ethical concerns and exposed the users to risks in terms of data protection. However, both data protection and ethical issues were considered and addressed within the engAGE project to guarantee users’ security and safety. Thus, the presented PoC should be followed by a larger structured RCT that involves a larger sample to appreciate the significant impact of the engAGE platform, including personalization functionalities, both on end users and on national health care systems.

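### Results and Summary promise efficacy from improved or maintained cognition, without tying this to the planned between-group comparison and against the article's own exploratory status

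*Protocol article*

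**What the plan says.** The Results section of the protocol article gives the basis for an efficacy conclusion: "The efficacy of the engAGE platform will be demonstrated on the basis of the improvement or maintenance of cognitive capacity". It attaches no definition of maintenance, margin, time point or comparator. The Summary in the Discussion adds that the PoC will show preliminary efficacy on maintaining cognition. It also says that a positive impact on quality of life, physical activity and sleep will be demonstrated.

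Other sections take a different position:
- **Data Analysis** treats efficacy outcomes as exploratory and all analyses as descriptive, and says "this study was not powered to detect statistical significance". It plans paired tests within each group, tests of change scores between groups, and effect sizes. Only participants with at least 80% adherence are analysed.
- **Study Design** says that "a formal sample size calculation was not performed".
- **Limitations** says of the 6-month duration that "it was unlikely to observe significant changes in cognitive capacity or the caregiver burden", and assigns demonstration of efficacy to future studies.

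**The concern.** A conclusion that can rest on maintenance, without a margin or a comparator, can be drawn from a null result. The article itself expects no significant change, so the result it regards as most likely could be reported as efficacy.

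The between-group comparison that could support a statement about the platform is planned in Data Analysis, but neither the Results sentence nor the Summary sentence refers to it. Analysis is reported as complete and publication is pending, so this wording bears directly on how the main result will be described.

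**Working it through.** **1. The plan's own figures.** There is no alpha, power, target effect or SD from which to derive the sample size, so only the arithmetic can be checked. The article says "the sample size for the PoC was set to 80 primary end users". Italy and Switzerland each have 20 EG and 10 CG, and "while in Norway, 20 subjects were equally assigned to the two groups". EG: 20+20+10 = 50. CG: 10+10+10 = 30. Total 80, as stated. For enrolment the article reports "40 (81.6%) of the total 49 older adults with MCI were assigned to the EG and 9 (18.4%) to the CG". 40/49 = 81.6% and 9/49 = 18.4%, as stated.

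**2. How often an inert platform meets the Results sentence.** Alpha is not stated; two-sided 5% is assumed. Maintenance is undefined, so three readings are tried.

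*Reading A: no significant decline in the EG (paired t test).* P(pass) = 1 − P(T < −t), where t is the 97.5% point on n−1 df and T is noncentral t with noncentrality −d√n. Here d is the true decline in SDs of the change score. At n=40, t = 2.023, and for d=0.2 the noncentrality is −0.2 × √40 = −1.265.

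| EG n | d=0 | d=0.1 | d=0.2 | d=0.3 |
|---|---|---|---|---|
| 50 (planned) | 97.5% | 90% | 72% | 45% |
| 40 (enrolled) | 97.5% | 91% | 77% | 54% |
| 20 (assumed adherent subset) | 97.5% | 94% | 87% | 75% |

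Where there is a true decline, fewer analysed participants make a pass more likely. The 80% adherence restriction can only reduce n.

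*Reading B: observed mean change of at least zero.* P(pass) = Φ(−d√n). This is 50% at d=0, and at n=40 it is 10% for d=0.2.

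*Reading C: EG not significantly worse than CG.* An inert platform passes 97.5% of the time. At 40 v 9 with true harm of 0.5 SD, the noncentrality is 0.5 × √(40×9/49) = 1.355. Harm is then detected 26% of the time, so the platform still passes about 74%.

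**3. The contrast with a comparative rule.** If efficacy required the EG to be significantly better than the CG in change, an inert platform would pass 2.5% of the time. Power for a 0.5 SD effect would be 57% at 50 v 30 and 26% at 40 v 9. The effect detectable with 80% power is (1.96+0.84) × √(1/n₁+1/n₂), about 0.65 SD at 50 v 30 and 1.03 SD at 40 v 9. A comparative rule therefore discriminates, but this study cannot demonstrate efficacy by it. That agrees with Data Analysis and disagrees with the Results sentence.

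**4. Selection on the outcome scales.** Entry required MAC-Q ≥25 and MoCA 21–25. *If* the screening MAC-Q is also the T0 score, and high scores mean more complaints (as the entry rule implies), the expected spurious fall is (1−r) × SD × φ(a)/(1−Φ(a)), with a = (25−mean)/SD. The inputs are assumptions: mean 24–28, SD 4–5, retest correlation r 0.6–0.8.
- Smallest (mean 28, SD 4, r 0.8): 0.31 points.
- Largest (mean 24, SD 5, r 0.6): 1.86 points.

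A second set of assumptions (mean 22–28, SD 4, reliability 0.7–0.9) gives 0.14–1.5 points. For MoCA, simulation with SD 3, reliability 0.7–0.9 and source mean 20–26 gives a shift between −0.7 and +0.7 points. It is upward if the source mean is above 23 and downward if below.

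**The case against.** The strongest reply is that the Results sentence is one line of summary, not a decision rule. The article nowhere says that a non-significant within-EG change will count as maintenance. Goal of the Study announces both intra- and intergroup analyses, and Data Analysis plans the between-group tests, calls the work descriptive and asks for caution with P values. Most of this stands, and it rules out several stronger readings that a reader might infer:

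- *The trial has no control comparison for efficacy.* Not so. The comparison is planned; the fault is that the efficacy sentences are not tied to it.
- *An inert platform would almost always succeed, so the conclusion is positive regardless.* The 97.5% needs zero true change and a significance-based definition of maintenance. It falls to 77% and 54% at n=40 with true declines of 0.2 and 0.3 SD, and to 50% under reading B with no change.
- *Regression to the mean will certainly improve MAC-Q.* This requires one score to serve for both screening and T0. The article lists recruitment and baseline evaluation as separate phases and does not say whether MAC-Q was repeated. If it was, and correlations between occasions are equal, the expected T0–T2 regression is zero.
- *The MoCA entry window biases towards success.* It is two-sided, so the direction depends on an unknown source mean.

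The imprecision with 9 controls is also already conceded in substance by the statement on power, so it is not a separate fault here.

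What the reply does not remove is the conflict of wording. The article says that efficacy will be demonstrated in one place, and calls it exploratory and leaves its demonstration to others elsewhere.

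**Conclusion.** The point holds as a contradiction in the stated basis for the efficacy conclusion. The Results and Summary sentences use confirmatory language, leave maintenance undefined and do not refer to the EG–CG comparison, while Data Analysis and Limitations treat efficacy as exploratory and not to be demonstrated here.

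Its size depends on what maintenance means: with zero true change an inert platform passes 97.5% of the time if it means no significant EG decline, and 50% if it means a non-negative mean change. Those figures rest on an assumed two-sided 5% level and a t-test model. The finding that maintenance alone cannot separate an effective from an inert platform needs no assumed SD or correlation. Regression to the mean on MAC-Q is a possible further contribution, conditional on the screening score serving as baseline. MoCA selection supports no directional claim.

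**What to change.** In Results, replace the efficacy sentence with:

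> Preliminary efficacy will be estimated, as an exploratory result, by the EG minus CG difference in change in MAC-Q and MoCA with its 95% CI; within-group changes are descriptive and will not be read as maintenance or efficacy.

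In the Summary, replace the clause predicting preliminary efficacy on cognitive function with a statement that the PoC will also estimate the between-group difference in cognitive change. For quality of life, physical activity and sleep, replace the promise of demonstration with *will be estimated*.

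The cost is wording only. The between-group comparison is already planned, so no new data are needed. The downside is a weaker claim, and the interval will be wide: with 40 v 9 and an assumed MoCA change SD of 2 to 3, its half-width is 2.012 × SD × √(1/40+1/9), or 1.48 to 2.23 points, before any loss to the adherence restriction.

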### Data Analysis

This subsection describes the measurements, statistical tests, and tools with which the data collected in the engAGE PoC were, and are still being, analyzed. The different types of data that were collected in the engAGE project are as follows:

Credentials: username, password, email address, and similar security information used for authentication and account access in different services of the platformPersonal data: first name, last name, gender, age, weight, height, email address, contact address, and phone number of older adults in different services of the platformAnswers to specific questions in self-assessment questionnaires on MEMASGames score from Pepper appsMeasurements and monitored parameters: weight, heart rate, blood pressure, and physical activities gathered through the monitoring infrastructureHistorical data of the measurements and monitored parameters for training and using ML algorithms for each older adult in the ML service

In the engAGE testing and evaluation phase, the following data were, and are being, processed:

Information and results from questionnairesCognitive game scoresHistorical data of measurements collected for each end userAny information the end users decided to share through discussions/interviews, as well as data providing feedback from trialsOutcomes that concern feasibility (ie, the primary interest of the engAGE PoC): recruitment rate (proportion of eligible individuals who consent to participate in the study, ie, those who attended more than 80% of weekly sessions), retention rate (proportion of participants who completed the 6-month intervention period), and adherence to the intervention (average number of interactions with the Pepper robot during weekly sessions, the frequency of use of the MEMAS app, and the activity tracker recording time)

Descriptive statistics (means, SDs, medians, IQRs) will be used to summarize adherence metrics.

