## Discussion

### Summary

The engAGE project is an innovative intervention designed to counteract cognitive decline in older adults with MCI by integrating social robots, mobile apps, and wearable sensors into a comprehensive platform. The presented PoC will demonstrate the feasibility of this approach that merges in-facility and at-home technology-based intervention in three European countries (Italy, Switzerland, and Norway). The PoC will also show preliminary efficacy in maintaining cognitive function, which is the primary goal of the engAGE platform. Moreover, a positive impact on the quality of life, physical activity levels, and sleep quality among participants will be demonstrated, as well as acceptability and usability rates of the platform. Regarding secondary end users, the introduction of the engAGE platform is expected to reduce caregivers’ burden and enhance their engagement in the care process.

The engAGE platform addresses critical gaps identified in previous studies on digital health interventions for MCI. Social robots have been explored for their potential to engage older adults with dementia or MCI [17,18]. Although these studies have demonstrated the acceptability of social robots for promoting social interaction and cognitive stimulation, they often focus on single-domain interventions (eg, storytelling or quizzes) rather than a holistic approach combining cognitive training, physical activity monitoring, and caregiver support. In addition, several mobile apps have been developed for cognitive training in older adults with MCI, such as those focused on memory games or problem-solving tasks [13,14]. However, these apps often lack integration with other tools or technologies that address physical activity or social engagement. Similarly, telehealth interventions have shown promise in providing remote cognitive rehabilitation, but they typically do not include real-time interaction [15,16]. In contrast to these existing solutions, engAGE offers a multicomponent intervention that integrates social robotics, mobile apps, and an activity tracker, as well as personalization by ML algorithms. Moreover, the innovative approach of the engAGE platform integrates in-facility services and home-based intervention. This comprehensive approach aligns with recommendations from recent systematic reviews emphasizing the need for multidomain interventions to address the complex needs of older adults with MCI [41,42].

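### Data Analysis and Results give non-overlapping bases for the feasibility conclusion, the Results basis appears confined to adherent participants, and the Discussion presumes the answer

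*Protocol article*

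**What the plan says.** All references are to the protocol article.

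- **Methods, Data Analysis** lists the outcomes that concern feasibility and labels them the primary interest. The first is a recruitment rate (consenting among eligible individuals, with a gloss about attending more than 80% of sessions). The second is the "retention rate (proportion of participants who completed the 6-month intervention period". The third is adherence, measured by how often people interacted with the robot, how often they used the app, and how long the tracker recorded. It adds: "Descriptive statistics (means, SDs, medians, IQRs) will be used to summarize adherence metrics".
- **The same section** says that only participants with at least 80% adherence entered the analysis. It then says that the same analyses were applied to the UTAUT and SUS scores, which "provided insights into the primary goal of the study: the feasibility of the intervention".
- **Methods, Study Design** also links acceptance and usability to understanding feasibility. It sets the sample at 80 (50 experimental, 30 control) on practical grounds: "a formal sample size calculation was not performed".
- **Results** states that "the feasibility of the engAGE intervention will be assessed on the basis of the usability and acceptance of the platform", both measured on standardised scales. It reports 49 enrolled, 40 experimental and 9 control, and mentions difficulties in organising the trial and recruiting.
- **Discussion, Summary** states: "The presented PoC will demonstrate the feasibility of this approach".
- **Safety and Security Considerations** says that all screening data were discarded once the project was complete.

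**The concern.** A feasibility study should draw its feasibility conclusion from the outcomes it named for that purpose. Here the sentence in Results that says how the conclusion will be reached uses none of them. Recruitment, retention and adherence are where a six-month programme of weekly robot sessions and daily home use would show difficulty. Usability and acceptance scores measure something else: what users thought of the platform.

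The apparent 80% adherence restriction makes this worse. If the scores come only from people who kept to the intervention, poor adherence reduces the number of scores but does not lower them. A reader planning the larger trial recommended under Limitations could then take over a feasibility statement that reflects neither who could be enrolled nor who stayed.

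**Working it through.** **1. The two bases side by side.**

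- Data Analysis, listed feasibility outcomes: recruitment rate, retention rate, adherence.
- Results, basis of the assessment: usability (SUS), acceptance (UTAUT).
- Measures in common: none.

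A later paragraph of Data Analysis connects the two sets by saying that UTAUT and SUS give insight into feasibility. That makes them contributors to the assessment and does not replace the listed outcomes.

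**2. Who supplies the Results measures.** Let q be the share of platform users with at least 80% adherence, m1 their mean score, and m0 the mean score of the others. The mean over all users is q·m1 + (1 − q)·m0. The restricted analysis reports m1. The difference is

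m1 − [q·m1 + (1 − q)·m0] = (1 − q)(m1 − m0).

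This grows as adherence falls, and it flatters the platform whenever adherent users rate it higher. The article gives neither q nor any score, so the amount cannot be computed.

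**3. Planned numbers reproduced.** The Recruitment section gives 20 + 10 in Italy, 20 + 10 in Switzerland (reading the 30 subjects as 30 in each country) and 10 + 10 in Norway.

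- Experimental: 20 + 20 + 10 = 50
- Control: 10 + 10 + 10 = 30
- Total: 80, with shares 50/80 = 62.5% and 30/80 = 37.5%, as stated.

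**4. Enrolment against plan.**

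- Overall: 49/80 = 61%, a shortfall of 31
- Experimental: 40/50 = 80%
- Control: 9/30 = 30%, a shortfall of 21

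**5. Splitting the control shortfall.** At the planned 37.5% share, 49 enrolled would give 49 × 0.375 = 18.4 controls.

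- Due to lower total enrolment: 30 − 18.4 = 11.6
- Due to departure from the planned allocation: 18.4 − 9 = 9.4

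So 9.4/21 = 45% of the control shortfall is not a recruitment effect. The experimental figure is raised by the same amount: 49 × 0.625 = 30.6 expected, 40 observed.

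Enrolment by country is not given. If k of the 49 came from Norway (equal allocation, at most 20 planned) and the rest from the 2:1 sites, the expected number of controls is k/2 + (49 − k)/3 = 49/3 + k/6. This runs from 16.3 (k = 0) to 19.7 (k = 20). The allocation part is therefore between 7.3 and 10.7, whatever the country mix.

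**6. Whether the listed recruitment rate can be computed.** Its denominator is eligible individuals, not the planned 80, so 49/80 is not that rate. If the count of eligible individuals was lost with the discarded screening data, the rate cannot be computed, and enrolment against target is the available substitute.

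**The case against.** The strongest reply is that the Results sentence is a short summary. It does not say that usability and acceptance are the sole basis, and it does not displace Methods. Study Design and Data Analysis let both sets of measures inform feasibility, and all analyses are declared descriptive. Enrolment is reported openly by arm. The Discussion verb is promotional wording, and Results itself already speaks of assessing. Control-arm numbers bear on the randomised design more than on the intervention, and the practical constraints in Study Design are reasons for choosing 80, not feasibility outcomes.

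Much of this stands. A reader might infer that the plan can only ever return a favourable verdict, or that the enrolment shortfall cannot alter the trial's primary conclusion. The documents do not support that:

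- Recruitment is a listed feasibility outcome.
- A descriptive assessment without a cut-off returns no automatic verdict in either direction.
- The full protocol is not shown and may hold progression criteria, so the absence of a threshold in the article is no finding.
- The article is not consistent about what is primary. Outcomes names cognitive capacity, and Data Analysis names both feasibility and the MAC-Q score.

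The reply does not remove the mismatch. The Results sentence is specific about its basis, omits every listed feasibility outcome, and relies on scores that appear to be restricted by adherence.

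**Conclusion.** The point holds as an inconsistency with a practical consequence. The article defines feasibility by one set of outcomes, says it will assess feasibility on another with no overlap, and presumes success in the Discussion. Following the Results sentence would leave out recruitment, retention and adherence, and would use a sample selected on adherence.

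The enrolment information at stake is 49 of 80 overall, 40 of 50 experimental and 9 of 30 control. It is tempting to read 9 of 30 as pure recruitment failure, but about 9 of the 21 missing controls reflect the allocation departing from plan. Confidence intervals on these fractions would mean nothing, because planned places are not a sample of independent trials.

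The conclusion rests on two readings: that the 80% adherence restriction carries over to SUS and UTAUT, which the order of the text suggests but does not state outright, and that the Results sentence is meant as the basis of the conclusion. If the restriction does not carry over, the selection argument falls and the mismatch remains.

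**What to change.** 1. **Results.** Base the feasibility assessment on the outcomes listed in Data Analysis. Report retention and adherence for all enrolled participants (the platform adherence measures apply to the experimental group). Present SUS and UTAUT as supporting measures for everyone with data, not only those with at least 80% adherence.
2. **Enrolment table.** Give enrolled against planned by arm and country, descriptively and without intervals on planned places. Note that the control figure combines under-recruitment with a departure from the planned allocation (about 18 expected among 49).
3. **Recruitment rate.** If the number of eligible individuals no longer exists, say that the rate defined in Data Analysis cannot be computed, and give enrolment against target instead.
4. **Discussion, Summary.** Say that the study will assess feasibility, not that it will demonstrate it.
5. **No threshold and no prescribed verdict.** The data are already in, so a pass mark chosen now would be post hoc. Estimates and counts are enough.

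The cost is rewording in two places and one extra descriptive table, with the possibility of a less favourable feasibility statement. Arm totals are already published. The country breakdown and the scores of less adherent participants are assumed to be on file.
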